### Data Collection

The following data will be collected for each enrolled participant: study site, registration date, gestational age, participant’s age, gravidity and parity, history of abnormal cervical cytology and lesions, past screening history and results, cytology and HPV testing results, colposcopic findings, biopsy results, delivery outcome, gestational age at delivery, and mode of delivery.

In addition, questionnaire-based data will include marital status, history of oral contraceptive use, smoking history, HPV vaccination history, and questions about health literacy. Immunocytochemistry data from cervical swab specimens will also be collected.

### Safety Considerations

The trial interventions are limited to cervical scraping and colposcopy; cervical biopsy is not included because it is performed according to routine clinical practice criteria. To date, no severe adverse pregnancy outcomes related to cytology brushes have been reported [18]. Adverse events will be recorded if they meet the following criteria: grade 3 or higher according to the Common Terminology Criteria for Adverse Events [19], including miscarriage, grade 2 bleeding, or any unplanned visit requiring treatment. Only adverse events occurring within 1 week of the procedure will be collected given that potential effects of the intervention are expected to be short-lived. At each participating site, the investigators will assess the relationship of each adverse event to the study procedure and record the information in the electronic data capture form, and the prespecified statistical analysis will be performed after data lock. However, any unexpected or severe adverse events considered related to the study procedure will be promptly reported to the ethics committee.

### Sample Size and Statistical Analysis

All enrolled participants who undergo cervical sampling during early pregnancy and have evaluable baseline screening results will constitute the full analysis set. A per-protocol set, defined as participants in the full analysis set without major protocol deviations affecting assessment of the primary end point, will be used for sensitivity analyses. CIN2+ case detection via the HPV testing protocol is defined as the number of CIN2+ cases detected in participants with ASC-US or worse and who are HPV-positive at baseline screening. CIN2+ case detection via the cervical cytology protocol is defined as the number of CIN2+ cases detected in participants with ASC-US or worse and who are HPV-positive plus those with LSIL or worse and who are HPV-negative at baseline screening. Because the difference in the number of CIN2+ detections between each protocol corresponds to participants with LSIL or worse or who are HPV-negative, which is expected to be minimal, this trial is designed to demonstrate the noninferiority of the HPV testing protocol [15]. Table 1 summarizes the expected HPV positivity rate, the CIN2+ detection rate, and the estimated numbers of HPV-positive cases and CIN2+ detections among 5000 participants in this trial, based on previous literature.

**Table 1 table1:** Expected proportions of each group classified by human papillomavirus (HPV) and cytology results and incidence of cervical intraepithelial neoplasia (CIN) 2 or worse.

Category			NILM^a^ and who are HPV-negative (%)		ASC-US^b^ and who are HPV-negative (%)		LSIL^c^ or worse and who are HPV-negative (%)			ASC-US and who are HPV-positive (%)		LSIL or worse and who are HPV-positive (%)			NILM and who are HPV-positive (%)
Proportion of each group in the overall population															
	Assumed proportion in this study	87.5		1		0.5			1		2			9	
	Range in previous studies [15,20,21]	85.1-89.4		0.7-1.2		0.7-1.2			0.6-1.4		0.7-2.9			7.4-10.8	
CIN2^+^ detection rate immediately after screening															
	Assumed proportion in this study	—^d^		—		8			13		26			—	
	Range in previous studies [15,22-25]	—		—		2.16-15.3			13-13.5		25.9-27.5			—	
	Estimated number per 5,000 participants	—		—		2			6.5		26			—	
Annual incidence of newly detected CIN2^+^															
	Assumed proportion in this study	—		0.3				—	3				—	1.5	
	Range in previous studies [23,24]	—		0.2-0.3				—	2.6-4.2				—	1.33-1.95	
	Estimated number per 5000 participants	—		0.2				—	4.5				—	6.8	

^a^NILM: negative for an intraepithelial lesion or malignancy.

^b^ASC-US: atypical squamous cells of undetermined significance.

^c^LSIL: low-grade squamous intraepithelial lesion.

^d^Not applicable.

The estimated detection rate of CIN2+ cases immediately after the baseline screening is 0.65% for the HPV testing protocol and 0.69% for the cervical cytology protocol [15,20-27]. Regarding the primary end point, the noninferiority margin was set at 0.132% assuming that HPV screening could detect an additional 0.132% of cases after 1 year. The target sample size was set at 5000 participants taking into consideration the possibility of accumulation. To ensure sufficient statistical power, the primary analysis will use a one-sided 10% noninferiority test using the method by Tango [28], and with 5000 cases, the study can achieve a statistical power of at least 80%. An interim analysis is not planned. The extent of missing data, including loss to follow-up, will be summarized descriptively. Study site characteristics will also be summarized, and their potential impact on the results will be considered as appropriate.

### Quality Assurance

Central monitoring will be conducted using data collected through an electronic data capture system. Queries will be generated as needed to ensure data accuracy and completeness. An audit will not be conducted because the study intervention is minimally invasive and considered low risk. Study conduct and data integrity will be ensured through centralized monitoring.

### Ethical Considerations

This trial was approved by the Ethics Committee for Life Science and Medical Research Involving Human Subjects at Yokohama City University on July 25, 2024 (approval F240704001), and the current protocol version is 1.2. The ethical and social acceptability of the study was reviewed by an institutional ethics committee that includes lay members, ensuring public oversight without direct patient and public involvement. The protocol and statistical analysis plan can be obtained from the study office at the Department of Obstetrics and Gynecology, Yokohama City University. Written informed consent will be obtained from all research participants who meet the eligibility criteria. Each participant will be assigned a unique study ID, anonymized data will be securely managed at the data center, and direct contact with research participants will be facilitated through a call center. Personal information will be used only for the identification of participants and for limited purposes, such as sending test kits and results or a gift card in compensation. This study may involve future secondary use of data and biological samples. Therefore, the participants will be informed of this possibility at the time of consent, and their agreement to such use will be confirmed. If the samples are to be used for additional research, a new research protocol will be prepared, which will be approved by the ethics committee, and an opt-out procedure will be implemented before use. A gift card valued at ¥500 (US $3.15) will be provided to participants as a token of appreciation for their participation. This study is registered in the Japan Registry of Clinical Trials under the clinical research implementation plan number jRCT1030240280, which was issued on February 26, 2025. Major changes to the protocol will be approved by the ethics committee, reported to the principal investigator, and reflected in the Japan Registry of Clinical Trials. The research plan and results will be published.

## Results

Funding for this study was provided in April 2024. The study protocol was approved by the ethics committee on July 25, 2024. Data collection commenced in September 2024 and is scheduled to be completed by December 2026. As of March 2026, a total of 1906 participants had been enrolled. Data analysis is currently planned to begin in December 2027, and the study findings are expected to be published in 2028.

## Discussion

In this study, the primary end point is to assess the noninferiority of HPV testing compared with cytology for detecting CIN2+ lesions during pregnancy. Secondary end points include evaluating whether participants who test negative during pregnancy remain negative post partum, thereby informing the appropriateness of screening intervals and examining the effect of false-positive results through events identified at 1 year of follow-up.

The NILM and HPV-positive group is eligible for 1-year follow-up only under the HPV testing protocol, whereas the ASC-US and HPV-negative group is eligible for 1-year follow-up only under the cytology screening protocol. However, in either group, if participants do not attend the 1-year follow-up visit, CIN2+ cases detected at that time may be underestimated. Importantly, these groups are not recommended to undergo additional diagnostic evaluation during the remainder of the pregnancy and, therefore, do not contribute to the CIN2+ detection rate during pregnancy. In this study, we focused on ensuring that missed CIN2+ cases under the HPV testing protocol are minimized in the unique clinical setting of pregnancy; therefore, the primary end point was defined as the noninferiority of the CIN2+ detection rate during pregnancy. On the basis of existing data, the HPV testing protocol is estimated to detect an additional 0.132% (6.6 of 5000) of CIN2+ cases within 1 year. Therefore, the noninferiority margin was set at 0.132%, assuming that a small number of cases not detected during pregnancy via the HPV testing protocol could be identified at follow-up. This margin is considered clinically acceptable in light of American Society for Colposcopy and Cervical Pathology guidance that immediate confirmatory evaluation is not required for populations with a risk of CIN grade 3 or higher of less than 0.4% [24]. Compared with the cytology protocol, the HPV testing protocol is expected to increase the number of individuals requiring repeat testing at 1 year by 8% (400/5000). In contrast, 87.5% (4375/5000) of the participants may be eligible for an extended screening interval from 2 to 5 years, which is expected to reduce the overall testing burden. Thus, if CIN2+ case detection during pregnancy via the HPV testing protocol is noninferior to that of the cytology protocol, introducing the HPV testing protocol would have substantial clinical value.

During pregnancy, the accuracy of cervical cytology may be compromised by increased mucus production and shifts in cervical position, and some cases of invasive cervical cancer missed through cytology have been reported. Although the comparable efficacy of cervical cytology between pregnant and nonpregnant cohorts has been described [29], baseline characteristics were not adjusted for. In contrast, HPV testing has demonstrated robust efficacy in the general population even when performed using vaginal swab samples rather than cervical swabs [30], suggesting that it is less affected by mucus production and cervical position. These findings indicate that HPV testing may be a reliable method for cervical cancer screening during pregnancy, with the additional potential benefit of extending screening intervals. However, the effectiveness of HPV testing has not been sufficiently validated.

The global HPV infection rate among pregnant women is an average of 30.8% [31], with considerable variation by region and age; in Japan, reported rates range from 6.1% to 32.5% [26,32]. Some studies have shown that HPV infection is more prevalent in pregnant women than in nonpregnant women of the same age group, which may be related to changes in immune status and sex hormone levels [33].

Validation in the pregnant population is essential because baseline characteristics may differ between the general and pregnant populations. Previous studies have indicated that HPV testing during pregnancy is feasible, with high lesion detection rates [34]. However, these studies did not use the HPV testing protocol that is currently used in many countries. Moreover, the required sample size and statistical power were not evaluated in advance.

To date, no statistically designed clinical trials have directly compared the effectiveness of HPV testing and cytology for cervical cancer screening during pregnancy. Trials require the enrollment of a large number of participants because cancer screening has an inherently low detection rate. Although large-scale prospective studies are often limited by financial and logistical challenges, this trial has secured sufficient funding and begun enrollment. The results of this trial will provide critical evidence to determine whether an HPV testing protocol should be adopted as the primary cervical cancer screening method in pregnant women because of its potential advantage of extended screening intervals or to determine whether the current cytology-based protocol should be maintained. However, this study has several limitations, including its single-arm design, short follow-up period, and the fact that biopsy decisions are based on real-world clinical practice and left to the discretion of the attending board-certified obstetrician-gynecologist. If a biopsy is not performed, this may introduce verification bias.

The findings of this study are expected to provide evidence to inform whether the HPV testing protocol should be introduced for pregnant women or whether the current cytology protocol approach should be maintained. The findings of this study will be widely disseminated through publication in peer-reviewed international journals and presentations at domestic and international academic conferences. In addition, as many institutions registered with the Japan Society of Obstetrics and Gynecology are participating in this study, we plan to use the knowledge gained from this study to advocate that the society develop cervical cancer screening guidelines for pregnant women.

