**Conclusions:**

The results of this trial will clarify whether the HPV testing protocol should be adopted as the primary cervical cancer screening method for pregnant women or whether cervical cytology should remain the standard of care.

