**Figure 1 figure1:**
[figure not shown]
Current cervical cancer screening protocol in Japan. In the human papillomavirus (HPV) testing protocol, HPV-negative cases are scheduled for another HPV test in 5 years. HPV-positive cases undergo cervical cytology. For cases positive for HPV and atypical squamous cells of undetermined significance (ASC-US), colposcopy with or without cervical biopsy is performed immediately. Repeat HPV testing is scheduled within 1 year for HPV-positive and negative for an intraepithelial lesion or malignancy (NILM) cases. In the cervical cytology protocol, cases that are NILM are scheduled for another cervical cytology 2 years later. Cases with ASC-US undergo HPV testing, and cervical cytology is scheduled 1 year later for cases with ASC-US and who are HPV negative. For cases with ASC-US and who are HPV positive or for low-grade squamous intraepithelial lesion (LSIL) or worse cases, colposcopy and cervical biopsy are performed immediately.

Pregnant women have been excluded from most HPV screening trials. Therefore, the efficacy of HPV screening in this population has yet to be determined. The aim of this trial is to evaluate the effectiveness of the HPV testing protocol compared with that of the cervical cytology protocol for cervical cancer screening in pregnant women.

A noninferiority trial design was selected for this study. The number of cervical intraepithelial neoplasia (CIN) grades 2 and 3, adenocarcinoma in situ (AIS), and invasive cervical cancer (hereafter abbreviated as CIN2+) cases detected during pregnancy is expected to be higher under the cytology protocol than under the HPV testing protocol as the cytology protocol includes a broader population for confirmatory colposcopic evaluation, making a superiority trial design for HPV screening infeasible. Large-scale studies in nonpregnant women have demonstrated that HPV testing is comparable or superior to cytology in detecting CIN and invasive cervical cancer. In addition, HPV testing allows for the extension of the screening interval when negative; therefore, even if lesion detection rates are similar, the HPV testing protocol offers meaningful clinical advantages.

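### The 0.132% margin is explained as later recovery of missed cases, but it is an exchange between different women: the CIN2+ cases the HPV protocol misses have no 1-year test

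*Protocol article*

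**What the plan says.** Sample Size and Statistical Analysis defines what each protocol counts. For the HPV protocol, "CIN2+ case detection via the HPV testing protocol is defined as the number of CIN2+ cases detected in participants with ASC-US or worse" who are also HPV-positive. The cytology protocol counts the same women "plus those with LSIL or worse and who are HPV-negative at baseline screening". The section itself places the difference between the protocols in that added group.

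The legend of Figure 1 says what happens next under the HPV protocol: "HPV-negative cases are scheduled for another HPV test in 5 years".

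The margin is explained twice. In Sample Size and Statistical Analysis, "the noninferiority margin was set at 0.132% assuming that HPV screening could detect an additional 0.132% of cases after 1 year". In the Discussion, "the HPV testing protocol is estimated to detect an additional 0.132% (6.6 of 5000) of CIN2+ cases within 1 year", and the margin is then set at that figure, "assuming that a small number of cases not detected during pregnancy via the HPV testing protocol could be identified at follow-up". The Discussion adds that the margin is clinically acceptable in view of a guideline threshold of 0.4% for the risk of CIN3 or worse.

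The Conclusions of the Abstract tie the result to policy: "The results of this trial will clarify whether the HPV testing protocol should be adopted as the primary cervical cancer screening method". The Discussion makes a similar link.

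**The concern.** A noninferiority margin bounds how much worse the new strategy may be. Here it bounds the CIN2+ cases that cytology finds in pregnancy and the HPV protocol does not. If the margin is defended on the ground that those cases turn up at follow-up, they must be in women who have a follow-up test under the HPV protocol. By the definitions above, they are not.

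What is at stake is the reading of a positive result. With the present rationale, a reader may take noninferiority to mean that missed lesions are found a year later, and so accept the margin as a short delay. What the margin allows is a loss in one group of women, offset by an expected gain in another group that the primary test does not examine. The adoption statement rests on the primary result, and nothing in the article makes it depend on whether that gain appears.

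**Working it through.** **1. The plan's detection rates.** Inputs from Table 1, per 5000 participants:
- ASC-US/HPV-positive: 5000 × 1% × 13% = 6.5
- LSIL or worse/HPV-positive: 5000 × 2% × 26% = 26
- LSIL or worse/HPV-negative: 5000 × 0.5% × 8% = 2

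HPV protocol: 6.5 + 26 = 32.5, or 0.65%. Cytology protocol: 32.5 + 2 = 34.5, or 0.69%. Both match the article. Every case counted for the HPV protocol is also counted for cytology, so the shortfall is exactly the CIN2+ cases in LSIL-or-worse/HPV-negative women: 2 expected, 0.04%.

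**2. The plan's margin.** The Discussion names the two groups whose 1-year visit belongs to one protocol only. With Table 1's annual rates:
- NILM/HPV-positive (HPV protocol only): 5000 × 9% × 1.5% = 6.75
- ASC-US/HPV-negative (cytology protocol only): 5000 × 1% × 0.3% = 0.15

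Net: 6.75 − 0.15 = 6.60, and 6.60/5000 = 0.132%. This matches. The rounded table entries, 6.8 − 0.2, also give 6.6.

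**3. The two groups side by side.** The women who make up the shortfall are LSIL or worse and HPV-negative. The women who make up the 0.132% are NILM/HPV-positive and ASC-US/HPV-negative. The sets do not overlap. Of the 2 cases expected to be missed, none has a scheduled 1-year test under the HPV protocol.

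**4. What the 0.132% means.** It is the loss in pregnancy at which cumulative detection at 1 year would be equal. Abnormal/HPV-positive women contribute 5000 × 3% × 3% = 4.5 further cases to both protocols. Expected totals through 1 year:
- HPV protocol: 32.5 + 6.75 + 4.5 = 43.75
- Cytology protocol: 34.5 + 0.15 + 4.5 = 39.15

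The difference is 4.6, which is the gain of 6.6 less the loss of 2.

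**5. Size of the margin.** 0.132/0.69 = 19% of the expected cytology yield; 6.6/2 = 3.3 times the expected loss.

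**6. How firm the 0.132% is.** Stacking all unfavourable, then all favourable, ends of the ranges in Table 1:
- Low: 7.4% × 1.33% − 1.2% × 0.3% = 0.095%
- High: 10.8% × 1.95% − 0.7% × 0.2% = 0.209%

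The figure also supposes that everyone attends at 1 year. If the same fraction attends in both groups (an assumption; the article gives none), the gain scales with it: 0.132% × 0.9 = 0.119%, × 0.8 = 0.106%, × 0.7 = 0.092%.

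**7. The test and the power claim.** Let b be the number of cytology-only cases. There can be no HPV-only cases, so Tango's statistic is Z = (5000 × 0.00132 − b)/√(5000 × 0.00132 × (1 − 0.00132)) = (6.6 − b)/2.567. At b = 3, Z = 1.402; at b = 4, Z = 1.013; the one-sided 10% critical value is 1.282. The trial passes if b is 3 or fewer. With b binomial (5000, 0.0004), exact power is 85.7% and the asymptotic formula gives 82.3%. The claim of at least 80% holds. The probability of passing is 10.5% if the true loss is 0.132% and 30% if it is 0.095%.

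**The case against.** The strongest defence is that the exchange is already disclosed. The Methods sentence speaks only of additional cases found after 1 year; it does not say that missed cases are recovered. The Discussion names the NILM/HPV-positive and ASC-US/HPV-negative groups in the same paragraph as the margin. CIN2+ in a NILM/HPV-positive woman is, literally, also a case not detected in pregnancy. The Discussion warns that non-attendance may lead to underestimation at 1 year, the follow-up section describes retention measures, and short follow-up is a listed limitation. The first secondary end point already compares the protocols in early pregnancy and 1 year later. The 0.4% benchmark is offered as context and not as a derivation. Within the trial, LSIL-or-worse/HPV-negative women do receive colposcopy and follow-up.

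Most of this stands, and it limits the point to the rationale and the inference drawn from it. It does not rescue the Discussion sentence. The margin bounds the shortfall against cytology, that shortfall lies only in HPV-negative women, and cases found in NILM/HPV-positive women are not part of it. The colposcopy given within the trial does not help either, because the margin has to justify the HPV protocol as it would be used.

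A reader might go further in three ways that the document does not support:
- That any true loss up to 0.132% would pass. It would usually fail: a loss at the margin passes with probability 10.5%, and the largest observed loss that passes is 3 cases, about 9% of 34.5.
- That the ranges in Table 1 show 0.132% to be wrong. It lies inside 0.095% to 0.209%, and those ends need every extreme to coincide.
- That the 0.4% benchmark can be converted into a tolerated share of the cytology yield. It is a CIN3+ risk and the yield is CIN2+, so the ratio has no meaning.

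**Conclusion.** The point holds as a defect in the stated rationale for the margin and in the conclusion built on it. The 0.132% is a break-even exchange: up to 6.6 CIN2+ cases per 5000 in HPV-negative women, 19% of the expected cytology yield, against 1-year cases in other women. It is not recovery of missed cases, because none of the women who form the shortfall has a 1-year test under the HPV protocol.

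This follows from the protocol's definitions and does not depend on any assumed rate. The size rests on Table 1's point assumptions. The break-even figure also needs full 1-year attendance.

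The margin arithmetic, the detection rates and the power claim all reproduce. It would be wrong to conclude that the margin or the sample size must change, or that trial participants go without evaluation.

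**What to change.** - In Sample Size and Statistical Analysis and in the Discussion, replace the rationale that relies on later identification. State that the margin accepts undetected CIN2+ in HPV-negative women in exchange for CIN2+ found at 1 year in other women, with the figures (6.6 per 5000, 19% of 34.5) and the attendance assumption.
- State that the 0.4% CIN3+ benchmark is context and does not derive a CIN2+ margin.
- Specify the 1-year comparison already listed under Secondary End Points as a cumulative (baseline plus 1-year) paired difference, HPV minus cytology, with confidence limits, as the key secondary analysis. Count each 1-year case only for a protocol that would have had the woman tested then, and report attendance by group.
- Rest any adoption statement, in the Abstract and in the Discussion, on the primary result together with that estimate. Otherwise limit the conclusion to detection in pregnancy. A rigid rule that the observed gain must equal or exceed the observed loss is not needed: it would have no error control, and non-attendance would bias it against HPV testing.

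The cost is wording and one specified analysis of data already being collected, and analysis is planned to begin only in December 2027. The downside is that the adoption claim then depends on one further result. Shrinking the margin instead would be costly: at 5000 participants and one-sided 10%, exact power falls to 67.7% at 0.10% and 40.6% at 0.08%.

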### Baseline Screening and Colposcopy or Biopsy During Early Pregnancy

Pregnant women will be recruited from prenatal care facilities in Japan, including those affiliated with the Yokohama Clinical Research Network.

After obtaining informed consent, cervical swab specimens will be collected at less than 17 weeks of pregnancy using the BD SurePath test with the Cytopick brush for both cervical cytology and HPV testing using the BD Onclarity assay. The results of HPV testing will be classified as high-risk HPV negative or high-risk HPV positive if they are positive for any of the evaluated genotypes (HPV16; 18; 31; 45; 51; 52; 33 and 58; 35, 39, and 68; or 56, 59, and 66).

The results of cervical cytology will be classified as follows according to the Bethesda system [16]: NILM, ASC-US, LSIL, atypical squamous cells cannot exclude a high-grade squamous intraepithelial lesion (HSIL; ASC-H), HSIL, squamous cell carcinoma (SCC), atypical glandular cells (AGC), AIS, and adenocarcinoma. LSIL or worse results include participants with LSIL, ASC-H, HSIL, SCC, AGC, AIS, adenocarcinoma, or other malignancies. ASC-US or worse results include participants with ASC-US, LSIL, ASC-H, HSIL, AGC, SCC, AIS, adenocarcinoma, or other malignancies.

Participants with an abnormal cervical cytology result, except for those with ASC-US and who are HPV negative, will undergo colposcopy and, if necessary, a cervical tissue biopsy.

CIN is classified according to the World Health Organization criteria as LSIL (CIN grade 1), HSIL (CIN grade 2), and HSIL (CIN grade 3) [17]. The primary end point, CIN2+ cases, is defined based on histological diagnosis of biopsy specimens by pathologists at each participating site using the same criteria. For participants requiring diagnostic evaluation, colposcopy is performed promptly, and the timing of this procedure is recorded in the case report form, allowing it to be clearly distinguished from the 1-year follow-up.

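### Discretionary biopsy in about 25 LSIL+/HPV-negative women decides the primary test, and any CIN2+ left unbiopsied there can only favour noninferiority

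*Protocol article*

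**What the plan says.** All places are in the protocol article.

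- **Biopsy.** Under Baseline Screening and Colposcopy or Biopsy During Early Pregnancy, women with abnormal cytology (other than ASC-US with a negative HPV test) "will undergo colposcopy and, if necessary, a cervical tissue biopsy". The same section defines CIN2+ by site pathologists' histology of biopsy specimens. The Discussion adds that biopsy is left to the attending specialist and that "If a biopsy is not performed, this may introduce verification bias".
- **Analysis set.** The section Sample Size and Statistical Analysis states that "All enrolled participants who undergo cervical sampling during early pregnancy and have evaluable baseline screening results will constitute the full analysis set". Histological verification is not a condition. A per-protocol set serves for sensitivity analyses.
- **Case definitions.** In the same section, the HPV protocol is credited with CIN2+ in women who are HPV-positive with ASC-US or worse. The cytology protocol is credited with those cases plus CIN2+ in women who are HPV-negative with LSIL or worse.
- **Margin and rates.** The expected detection rate "is 0.65% for the HPV testing protocol and 0.69% for the cervical cytology protocol", and "the noninferiority margin was set at 0.132% assuming that HPV screening could detect an additional 0.132% of cases after 1 year".
- **Missing data.** "The extent of missing data, including loss to follow-up, will be summarized descriptively".
- **Biopsy under each protocol.** The Introduction and the Figure 1 legend describe colposcopy together with biopsy for LSIL or worse under the cytology protocol. Under the HPV protocol they describe colposcopy with biopsy optional.

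**The concern.** The cytology protocol's cases are the HPV protocol's cases plus one extra cell. The comparison therefore rests on how many CIN2+ lesions are confirmed in that cell. A lesion there that is not biopsied stays in the denominator and adds no case, so the HPV protocol appears to have missed nothing. No opposing error can offset this, because an unbiopsied lesion in an HPV-positive woman is lost to both protocols equally.

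The article names verification bias as a general limitation. A reader could take it to be neutral or conservative, when it runs towards the conclusion the trial hopes to reach. The result is meant to inform screening guidelines for pregnant women, so the direction matters.

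**Working it through.** **Inputs.** n = 5000, margin D = 0.132% (5000 × 0.00132 = 6.6 cases), one-sided 10% Tango test. Expected rates are 0.65% and 0.69% (32.5 and 34.5 cases, difference 2). From Table 1, the LSIL+/HPV-negative group is 0.5% of participants (25 women) with 8% CIN2+ (2 cases).

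**The test under these definitions.** Let c be the number of CIN2+ cases found only by the cytology protocol, and b the number found only by the HPV protocol. By definition b = 0. For c below 6.6, the restricted estimate in Tango's score test equals D, and

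Z = (6.6 − c) / √(6.6 × 0.99868) = (6.6 − c) / 2.567, with critical value 1.2816.

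| c | Z | one-sided p | noninferior? |
|---|---|---|---|
| 0 | 2.571 | 0.005 | yes |
| 1 | 2.181 | 0.015 | yes |
| 2 | 1.792 | 0.037 | yes |
| 3 | 1.402 | 0.080 | yes |
| 4 | 1.013 | 0.156 | no |

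The rule is therefore to pass if c ≤ 3. Cases found by both protocols do not enter the statistic.

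**The plan's own figure.** With c ~ Bin(5000, 0.0004), P(c ≤ 3) = 85.7% (82.3% by normal approximation). This agrees with the stated power of at least 80%, so this is the intended test.

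**Effect of incomplete verification.** Let v be the share of true CIN2+ cases in the LSIL+/HPV-negative group that are histologically confirmed. The article gives no value, so v is an assumption. With the true loss at the margin, P(noninferior) = P(Bin(5000, 0.00132 × v) ≤ 3).

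| v | expected confirmed cases | P(noninferior) |
|---|---|---|
| 100% | 6.60 | 10.5% |
| 90% | 5.94 | 15.6% |
| 80% | 5.28 | 22.8% |
| 70% | 4.62 | 32.2% |
| 50% | 3.30 | 58.0% |

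**How plausible is a loss this large?** In the planned 25 women, 6.6 true cases would be a risk of 6.6/25 = 26%, against a Table 1 range of 2.16% to 15.3%. At 15.3% there would be 25 × 0.153 = 3.8 cases, inside the margin. A loss above the margin needs a larger or higher-risk group than planned. For example, the upper ends of both Table 1 ranges give 5000 × 0.012 × 0.153 = 9.2 cases.

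**The case against.** The strongest reply is that the end point is a count of cases diagnosed right after screening. The 0.65%, 0.69% and 0.132% are all detection figures, so they already carry whatever biopsy practice lay behind their sources. On that scale the test keeps its error at about 10.5%. This stands, and it rules out a flat claim that the type I error is inflated. It does not dispose of the point. The Primary End Point section speaks of true positive CIN2+, and the Discussion gives the aim as keeping missed CIN2+ to a minimum. Under-ascertained cases cannot show that.

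Other parts of the reply:

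- **Which women matter.** A reader might infer that every unbiopsied woman pushes the result towards noninferiority. Only those who actually have CIN2+ do so, about 2 of 25 at planned rates. All of these women have colposcopy, and if biopsy follows colposcopic suspicion, v may exceed the proportion biopsied.
- **A trial with no CIN2+.** It would pass (Z = 2.571), and a reader might take that as proof that the test is empty. With 34.5 cases expected, zero has probability of about 10⁻¹⁵. It is also a general property of an absolute margin: zero discordant cases in 5000 gives an exact one-sided 90% upper limit of 0.046%, below 0.132%.
- **Blinding.** The article is silent on whether clinicians know the HPV result when deciding on biopsy. Silence does not show that they do, and the argument does not need it.
- **The unseen analysis plan.** It may already contain sensitivity analyses, so their absence from the article is no fault. The histology-based count, the analysis set and the unstated direction of the bias are fixed in the article itself.
- **Existing safeguards.** These women are re-examined every 3 to 6 months and at 1 year, and the 1-year comparison is a secondary end point. That helps, but it does not feed into the primary result. The per-protocol set helps little: a permitted decision not to biopsy would probably not be a deviation, and excluding the woman adds no case.

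**Conclusion.** The point holds in a bounded form. The primary result turns on confirmed CIN2+ in about 25 women, with 3 cases passing and 4 failing, and unverified CIN2+ in that group can only favour noninferiority. The article discloses the bias but not its direction.

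The rise from 10.5% to between 16% and 58% rests on three conditions: the margin is read as a loss of true CIN2+, the true loss is 0.132%, and verification is between 90% and 50%, which are assumed rates. That loss also requires a larger or higher-risk group than planned. On the detection scale the nominal error is kept.

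Separately, the Introduction and the Figure 1 legend pair colposcopy with biopsy for LSIL or worse under the cytology protocol, whereas the baseline procedures make biopsy conditional. The comparator as run may therefore detect less than the comparator as described, in the group that decides the test. These passages must be reconciled. Which rule is right is not a matter for this review.

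**What to change.** 1. State in the limitations that verification bias in this design runs towards noninferiority.
2. Prespecify a sensitivity analysis of the primary end point that adds, as cases, LSIL+/HPV-negative women without baseline histology whose later histology up to 1 year shows CIN2+. Add a tipping-point count: with c confirmed cases (c ≤ 3), how many unbiopsied LSIL+/HPV-negative women would need to have CIN2+ to reach 4, that is 4 − c, set against the number left unbiopsied. Describe noninferiority as robust only if it survives.
3. Report biopsy rates by HPV status among women with LSIL or worse.
4. Reconcile the descriptions of biopsy under the cytology protocol.

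The miss fraction (HPV-negative CIN2+ over all cytology-protocol CIN2+) with an exact upper limit may be reported as supportive only. It guards against low ascertainment overall, not against selective under-biopsy. Judged against 0.132/0.69 = 19.1%, with 6.6 true cases in the deciding group and half of them verified, it would still pass 39% to 54% of the time, depending on the number of shared cases (27.9 to 32.5).

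**Cost.** Some wording and extra analysis on data already being collected, with time to settle it before the analysis planned for December 2027. The noninferiority claim may come out less firm, and later histology may include some incident lesions that were absent at screening.
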